### Assignment of interventions: blinding

#### Who will be blinded {17a}

Given the heterogeneity in the administration of the intervention and control arms, participants and clinicians will not be blinded. The research assistants assigned to code observational measures in assessments will be blinded to participants’ treatment assignments.

#### Procedure for unblinding if needed {17b}

Intentional unblinding will not occur for research assistants coding observational measures; if a research assistant unintentionally discovers a participant's allocation while watching a video, the video will be assigned to a different research assistant.

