Two pilot studies have been conducted to evaluate BRIDGE [35, 36]. In a pre-post feasibility study, mothers with depression (*n* = 28) completed an in-person, 16-week trial of BRIDGE [36]. The intervention demonstrated good feasibility, with high retention (86% retention) and significant reductions in maternal depression (*d* = 1.02) and child MI (*d* = 1.08). In focus groups conducted at post-test, participants indicated that they were generally satisfied with the program [36]. Mothers expressed that they found the parenting skills complementary to the DBT skills, with one participant stating, “Because I understood the DBT language… it made it easier for me to understand it when we did it with children and the way it applies is just amazing.” In compliance with public health recommendations to reduce in-person contact and physical distance during the COVID-19 pandemic, a second pilot study was run to evaluate the efficacy of BRIDGE delivered via telehealth using asynchronous psychoeducational videos alongside synchronous weekly group sessions [35]. Participants (*n* = 39) showed significant reductions in child MI symptoms (*d* = 0.41), maternal depression (*d* = 1.13), and parenting stress *(d* = 0.39) from pre- to post-intervention [35]. Retention was high, with 92.3% of mothers completing the program [35]. Given these favorable results, further research comparing BRIDGE to other available programs is necessary to expand services to mothers in need.

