#### Exploratory outcomes

Exploratory outcomes of this study include the mean change in family relationship quality from pre- to post-intervention, which will be assessed using self-report questionnaires measuring parenting qualities and strategies used by mothers, family support, and co-parent relationship quality. Additionally, mean change in maternal mental health symptoms will be assessed using self-report questionnaires measuring symptoms of various mental illnesses. Participants will also be asked to report on their recent exposure to stressful life events. Health and social service use will also be assessed at pre- and post-intervention.

In the intervention groups, we will measure participants’ engagement in program components, such as attendance to group and self-reported video watching (in the BRIDGE group).

Additional exploratory outcomes will consist of observational data of maternal sensitivity and child emotion regulation, measured by a virtual Zoom assessment with mothers and their children. Exploratory outcomes will also include co-parent mental health and parenting, and physiological indices of well-being (e.g., sleep and daily activity) collected using wearable Fitbit watches for monitoring participants’ heart rate.

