Program engagement will be assessed in a variety of ways. In both the BRIDGE and DBT Skills-only groups, clinicians will take attendance during therapy sessions. In the BRIDGE group, we will extract aggregate data on the number of views on the psychoeducational videos using Google Analytics. At T2, we will ask participants in the BRIDGE group to report about their use of the videos, homework assignments, and mood tracking throughout the intervention.

Exploratory outcomes will be assessed using observational measures of maternal sensitivity and child emotional regulation through virtual assessment videos. Maternal sensitivity will be coded using the Maternal Q-Sort developed by Pederson and colleagues [68]. Child emotions will be coded using a coding scheme developed by our research team. Child emotion codes were created in a systematic nature based on similar virtual assessments conducted by our team in the past. Codes include observations of children’s emotional cues (e.g., frowning, smiling) and verbal statements (e.g., “I hate this game,” “That was the best game!”) during and following an emotion-inducing task. Trained undergraduate coders will be required to reach 70% reliability on five separate videos when compared to an expert coder (Cronbach’s intra-class coefficient) [69] before coding independently. A total of 25% of all video segments coded will be double-coded by an expert coder to ensure the team maintains a reliability of 70% or higher.

An additional exploratory outcome includes physiological indices of well-being, which will be measured using Fitbit devices to monitor heart rate, sleep quality and duration, and physical exercise throughout the intervention’s duration. Finally, co-parent mental health and relationship quality will be measured via questionnaires (PHQ-9, CBCL, PSI-SF, CSI-4, MSPSS, CCNES, Parenting Scale Overreactivity, SCS-SF, GAD-7, PROMIS Anger, RSE, PROMIS Sleep, AUDIT, and CUDIT).

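### Passing a T2 video that reveals the mother's arm to another coder does not restore blinding, because the cue stays in the recording

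*Protocol article*

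**What the plan says.** All statements are in the Protocol article.

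- Who will be blinded {17a}: "participants and clinicians will not be blinded", whereas "The research assistants assigned to code observational measures in assessments will be blinded to participants’ treatment assignments".
- Procedure for unblinding if needed {17b}: if a coder accidentally learns a participant's "allocation while watching a video, the video will be assigned to a different research assistant". The section adds that coders will not be unblinded on purpose. It gives no other step for a video that has revealed the arm.
- Outcomes {12}, Exploratory outcomes: "Additional exploratory outcomes will consist of observational data of maternal sensitivity and child emotion regulation", taken from a Zoom session with mother and child.
- Plans for assessment and collection of outcomes {18a}, Exploratory outcomes: "A total of 25% of all video segments coded will be double-coded by an expert coder", so that coder reliability stays at 70% or above. The child codes include what the child says as well as visible emotional cues.
- Trial design {8}: these two measures are taken at T1 and T2 only.

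**The concern.** The rule in {17b} addresses discovery of the arm during viewing, and its remedy is a new viewer for the same video. If the mother or child says or shows something that identifies the arm, a change of viewer leaves the cue where it was. The second coder is exposed to it as well, and applying the rule again would call for a third.

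What is at stake is the credibility of the blinded coding. Both primary outcomes (PHQ-9 and CBCL) and both secondary outcomes (parenting stress and harsh parenting) are reported by mothers who know their arm. The coded measures are the only ones for which blinded assessment is claimed. The hypothesis for them is directional, with BRIDGE expected to do better than DBT and SAU (Objectives {7}), so a coder who knows the arm could lean towards the expected result. A video handled under the present rule would be counted as blind-coded although it may not have been, and no stated flag would let a reader tell which videos these are.

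**Working it through.** No arithmetic decides this point. The sections were set side by side.

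1. **Which videos can reveal the arm?** Under Screening and enrollment, the T1 Zoom assessment comes before the pre-intervention questionnaire. Under Implementation {16c}, mothers learn their arm only after completing the baseline questionnaires. A T1 video therefore cannot disclose the allocation. Only T2 videos are exposed.

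2. **When does reassignment work?** There are two cases.
   - The cue is specific to the first coder, for instance because the coder recognises the mother. A different coder does not share that knowledge, and the rule restores blinding.
   - The cue is in the content of the recording. Every viewer of that content is exposed, and the rule does not restore blinding.

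   The wording of {17b} covers both cases and gives both the same remedy. Discovery in the course of viewing fits the second case most naturally.

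3. **Does double-coding repair it?** The 25% second coding in {18a} tests agreement. Two coders who meet the same cue can agree and share the same expectation, so adequate reliability is no evidence that blinding held.

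4. **Could a T2 video carry such a cue?** By T2 the BRIDGE and DBT mothers have been offered 16 weeks of skills training (Intervention description {11a}). A mention of the parenting videos or the parent peer coach would point to BRIDGE, since the description of the DBT arm contains neither. An SAU mother also knows her arm and could say that she was not offered a group. Disclosure is thus possible in any arm. The article gives nothing from which to judge how often it happens.

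5. **How many videos?** The ceiling is one T2 session per participant, 3 × 60 = 180, if every mother opts in and stays to T2. The assessment is opt-in (Participant timeline {13}), so the true number of T2 videos is lower. The article gives no opt-in rate and no disclosure rate. The number affected lies somewhere from 0 to that ceiling and cannot be narrowed further.

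6. **How much can still be changed?** At the time of the article (Trial status), 78 of 180 had been randomised and first-round post-intervention assessments were under way. That leaves 180 − 78 = 102 participants to be randomised, with two further rounds planned.

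**The case against.** The strongest reply has four parts.

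**The article is condensed, and masking belongs in a coding manual.** This stands in part. The article does not say that the file is passed on unedited, and the scored segments may not contain the disclosure. But {17b} states a rule and names reassignment as the response. As written, that response fails for a cue in the content, so the point does not rest on silence alone.

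**The rule works for some cues.** This stands. Research assistants run the Zoom sessions and notify mothers of their arm, so recognition of a mother by a coder is a real possibility, and reassignment deals with it.

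**The outcomes are exploratory and the assessment is optional.** This stands. No primary or secondary conclusion depends on them.

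**The problem is easily overstated.** This also stands, and four stronger readings should be set aside.
- A reader might infer that the blinded outcomes as a whole are coded unblinded. T1 videos and T2 videos without a cue keep their blinding.
- A reader might infer that disclosure will be common and confined to the active arms, citing the pilot participant's remark that begins "Because I understood the DBT language" (Background and rationale {6a}). That remark comes from a post-test focus group about the programme, not from a mother-child task. BRIDGE and DBT teach the same four skill domains, so such vocabulary would not separate those two arms. SAU mothers may use any other service, so it would not reliably separate them from the active arms either.
- A reader might put a disclosure rate on the problem. None has a source in the article.
- A reader might call the videos the only check on maternal reporting bias. Fitbit data and co-parent questionnaires, which include the CBCL, do not rest on the mother's report either, although no blinding is described for them.

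**Conclusion.** The point holds in a narrow form. For T2 videos whose content reveals the arm, reassignment under {17b} does not restore coder blinding. This rests on one assumption, that at least some accidental discoveries come from what is seen or heard in the recording. It does not require a particular frequency or an imbalance between arms.

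The consequence is confined to maternal sensitivity and child emotion regulation, both exploratory. Its size is unknown, and neither the amount nor the direction of any resulting bias can be calculated from the article. It still merits correction, because blinded assessment is claimed for these outcomes alone and a better rule costs little.

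**What to change.** Revise {17b}, or the coding procedure it summarises, along these lines.

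1. When a coder learns the arm from the content of a video, that coder, who is already unblinded, mutes or cuts the disclosing segment if no scored material is lost. Only the masked file goes to the new coder.
2. Where masking would remove scored material, the video is coded, flagged as unblinded, and kept. The outcome is reported with and without flagged videos, and the number flagged is given by arm.
3. Simple reassignment remains for cues specific to the first coder.
4. T2 Zoom sessions not yet held open with a short scripted request not to mention the programme or group assignment.

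Existing staff can do this: a sentence or two in the coding procedure, a line in the session script, and minutes of editing per affected video. There are two limits. First-round T2 sessions already held cannot benefit from the script, although masking and flagging can still be applied to any recording not yet coded. Because verbal statements are themselves scored, masking may cost a few seconds of material, which is why the flagging route is needed.

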### Data collection and management

#### Plans for assessment and collection of outcomes {18a}

##### Primary outcomes

Depressive symptoms will be measured using the PHQ-9 [39]. The PHQ-9 is a 9-item self-report questionnaire with possible scores ranging from 0 to 27, with higher scores indicating greater symptom severity. Scores ≥ 10 will be considered clinically significant. The PHQ-9 has been used extensively for depression screening and demonstrates high specificity (92–94%) for identifying depression in mothers of young children [47]. Changes in child MI symptoms will be assessed using the Child Behaviour Checklist (CBCL) [48]. The CBCL is a parent-report questionnaire that measures child functioning across internalizing and externalizing symptoms. This measure also includes a Total Problem Score (TPS) as well as externalizing and internalizing problem scales. Higher scores on each of these subscales indicate a greater degree of child behavior and emotional problems. Possible scores on the TPS scale range from 0 to 200. The CBCL has demonstrated good validity and reliability [48]. It is one of the most widely used rating scales for child psychopathology and behavior and is a useful screener for childhood psychiatric disorders [49, 50].

##### Secondary outcomes

Parenting stress will be measured using the Parenting Stress Index-Short Form (PSI-SF) [51]. The PSI-SF is a self-report questionnaire that requires respondents to answer questions regarding their overall experience with parenting stress using a 5-point Likert scale ranging from 1 (*strongly disagree*) to 5 (*strongly agree*). Possible total scores range from 36 to 180, with scores above 90 indicating clinically significant distress [51]. The PSI-SF has been demonstrated to have good validity, test–retest reliability, and high internal consistency and is useful in clinical applications with mothers of young children [51, 52]. Harsh parenting will be measured using the Overreactivity subscale of the Parenting Scale [53]. The Overreactivity subscale contains 10 items related to harsh parenting behaviors. Harsh parenting includes expressing inappropriate anger, irritability, or meanness towards one’s child. Each item contains a parenting situation (e.g., “When my child misbehaves…”) and ask parents to rate how they would respond on a 7-point scale, using bimodal anchors that represent effective (e.g., “I speak to my child calmly”) and ineffective (e.g., “I raise my voice or yell”) parental responses. The Overreactivity subscale has strong internal consistency and responses have been demonstrated to correlate with child behavior problems in diverse populations [53].

##### Exploratory outcomes

Family relationship quality will be measured using the Couples Satisfaction Index (CSI-4) [54], the Multidimensional Scale of Perceived Social Support (MSPSS) [55], and the Coping with Children’s Negative Emotions Scale (CCNES) [56]. The CSI-4 is a 4-item scale with excellent internal consistency (0.90) and convergent and divergent validity in samples of women with depression [57]. The 12 items on the MSPSS demonstrate good internal reliability (0.88) [58]. The 6 subscales that make up the CCNES have acceptable internal reliability, ranging from 0.69 to 0.85 [56].

Maternal mental health will be measured using a variety of self-report measures including the Self-Compassion Scale-Short Form (SCS-SF) [59], the Generalized Anxiety Disorder 7-Item Scale (GAD-7) [60], the Patient-Reported Outcomes Measurement Information System (PROMIS) Anger Short Form (SF) [61], the PROMIS-Sleep Disturbance Subscale SF [62], the Alcohol Use Disorder Identification Test (AUDIT) [63], the Cannabis Use Disorder Identification Test (CUDIT) [64], and the Recent Stress Experiences checklist. The SCS-SF contains 12 items and shows strong internal consistency (0.86) [59]. The GAD-7 is a 7-item scale with strong internal consistency (0.89) [65]. The PROMIS Anger SF is a 5-item scale with strong internal consistency (0.90), as well as moderate convergent validity with other measures of aggression (*r* = 0.51) [61]. The PROMIS Sleep Disturbance SD contains 8 self-report items relating to participants’ sleep quality [62]; it has demonstrated strong psychometric properties in a variety of clinical and non-clinical populations [66]. AUDIT is a 10-item questionnaire with strong internal consistency (0.85) [67]. The CUDIT consists of 8 items with an internal consistency of 0.91 [64]. The RSE was developed by authors, based on recommendations from the JBP Research Network on Toxic Stress at Harvard’s Center on the Developing Child, to measure familial exposure to various stressors which may affect participants.

An additional scale created for use in this project will assess health and social service utilization. The scale asks about the number and type of participant experiences with various health and social services (e.g., hospital visits, Child and Family Services contacts, visits to the public library) in the previous 3 months.

Program engagement will be assessed in a variety of ways. In both the BRIDGE and DBT Skills-only groups, clinicians will take attendance during therapy sessions. In the BRIDGE group, we will extract aggregate data on the number of views on the psychoeducational videos using Google Analytics. At T2, we will ask participants in the BRIDGE group to report about their use of the videos, homework assignments, and mood tracking throughout the intervention.

Exploratory outcomes will be assessed using observational measures of maternal sensitivity and child emotional regulation through virtual assessment videos. Maternal sensitivity will be coded using the Maternal Q-Sort developed by Pederson and colleagues [68]. Child emotions will be coded using a coding scheme developed by our research team. Child emotion codes were created in a systematic nature based on similar virtual assessments conducted by our team in the past. Codes include observations of children’s emotional cues (e.g., frowning, smiling) and verbal statements (e.g., “I hate this game,” “That was the best game!”) during and following an emotion-inducing task. Trained undergraduate coders will be required to reach 70% reliability on five separate videos when compared to an expert coder (Cronbach’s intra-class coefficient) [69] before coding independently. A total of 25% of all video segments coded will be double-coded by an expert coder to ensure the team maintains a reliability of 70% or higher.

An additional exploratory outcome includes physiological indices of well-being, which will be measured using Fitbit devices to monitor heart rate, sleep quality and duration, and physical exercise throughout the intervention’s duration. Finally, co-parent mental health and relationship quality will be measured via questionnaires (PHQ-9, CBCL, PSI-SF, CSI-4, MSPSS, CCNES, Parenting Scale Overreactivity, SCS-SF, GAD-7, PROMIS Anger, RSE, PROMIS Sleep, AUDIT, and CUDIT).

##### Descriptive measures

Descriptive measures to be collected include socioeconomic and demographic information including age, highest level of education (high school diploma or lower vs. post-secondary education), household income, marital status (married or in a common-law relationship vs. other), number and ages of all children, and type of residential community (e.g., urban area vs. rural area). Additionally, we will collect information from mothers about the history and severity of their depression (e.g., age of onset, length of episodes). We will also collect information about the target child’s health, including information about their birth, physical health, mental disorder diagnoses, and medication use.

#### Plans to promote participant retention and complete follow-up {18b}

Participants will receive weekly email or SMS text reminders containing information for telehealth sessions. Participants will receive an additional $10 CAD if they complete the post-intervention and follow-up surveys in a timely manner.

#### Data management {19}

REDCap is managed by The Centre for Healthcare Innovation which acts as a hired consultant on the proposed study and will facilitate secure data collection and management. RCT data will be stored on a secure server in accordance with the University of Manitoba’s PHIA policies.

#### Confidentiality {27}

In accordance with the University of Manitoba ethics guidelines, participant confidentiality will be maintained through all phases of the study. All data from the study will be accessed exclusively by research team members who are trained in the University of Manitoba ethics protocols have completed training on the Public Health Information Act, and have taken an oath of confidentiality.

Assessment data will be stored on REDCap or password-protected University of Manitoba data servers. Documents containing identifying information will be stored securely on password-protected University of Manitoba data servers and will be accessed by a limited number of research coordinators. Questionnaire, Fitbit, and assessment data will be linked to de-identified participant ID numbers.

Telehealth sessions will be hosted on the secure Zoom Healthcare platform and will be password protected. Due to the group-based nature of the interventions, participant anonymity during sessions cannot be guaranteed. During the orientation session, clinicians will outline the potential limits to confidentiality and anonymity. Participants will be asked to share only their first names, avoid sharing about other members of the group with anyone outside of the group, and attend sessions from a private location. Further, telehealth sessions will not be recorded or included in assessment, although attendance and client notes will be recorded and stored.

#### Plans for collection, laboratory evaluation, and storage of biological specimens for genetic or molecular analysis in this trial/future use {33}

Not applicable. No biological specimens will be collected.

## Statistical methods

### Statistical methods for primary and secondary outcomes {20a}

Analyses for primary and secondary outcome variables, as well as exploratory outcome variables, will compare the changes over time between (a) the BRIDGE vs SAU groups and (b) BRIDGE vs DBT-only groups, each at *a* = 0.025 (combined type I error rate to 0.05). Linear models accounting for pre-intervention scores will be used as the primary analysis method. The persistence of effects at the 6-month follow-up will be examined using time-by-intervention interactions in a linear mixed-effects model, accounting for within-subject serial correlations and between-subject effects of the intervention and covariates. Standardized effect sizes for linear mixed models will be derived based on recommendations for linear mixed models [70, 71]. Standardized effect sizes of 0.20, 0.50, and 0.80 will be used to interpret small, medium, and large effects, respectively [70]. The research team will also investigate if there is baseline moderation by symptom severity to examine whether the BRIDGE intervention is more effective than the DBT-only or SAU interventions for participants who have higher symptom levels at pre-intervention.

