### Objectives {7}

The current study will expand on previous evaluations of BRIDGE by conducting a randomized controlled trial (RCT) comparing (1) BRIDGE (DBT skills training + Parenting Skills), (2) DBT (DBT skills training only), and (3) services as usual (SAU). Our primary aim is to examine the effects of BRIDGE on maternal depression and child MI symptoms. We hypothesize that participants who receive the BRIDGE and DBT interventions will report fewer depressive symptoms than participants in the SAU group. Participants who receive the BRIDGE intervention are hypothesized to report fewer child MI symptoms than those in the DBT and SAU groups. Our secondary aim is to evaluate the efficacy of BRIDGE in reducing parenting stress and harsh parenting. Participants who receive the BRIDGE intervention are hypothesized to show lower levels of parenting stress and harsh parenting than those in the DBT and SAU groups.

Additional aims of the RCT are to examine the effects of BRIDGE and DBT on family relationships, other service use (e.g., hospital visits, interactions with police), and maternal psychopathology symptoms. We hypothesize that mothers who receive the BRIDGE or DBT intervention will report lower psychopathology symptoms, reduced service use, and improved family relationship quality. We will also assess participants' engagement in each intervention.

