### Interventions

#### Explanation for the choice of comparators {6b}

The SAU condition of the study is intended to account for potential changes in depressive symptoms and other outcomes over time [40]. When compared to the BRIDGE and DBT-only conditions, the SAU condition will provide insight into whether either intervention is associated with improved outcomes (e.g., reduced depressive symptoms and parenting stress). The DBT condition will provide evidence about the benefits of providing both mental health and parenting support to mothers with MI. We are interested in examining differences in child MI symptoms and parenting stress and behaviors between participants exposed to the BRIDGE versus DBT interventions.

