### Outcomes {12}

#### Primary outcomes (the specific measures utilized are described below in data collection and management)

The primary outcome of this study is mean change in depressive symptoms in mothers from pre- to post-intervention as measured by a self-report questionnaire [39]. Another primary outcome of this study is mean change in child behavioral problems from pre- to post-intervention, measured by parent-report questionnaire [47].

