### Sample size {14}

A sample size of 180 participants will be sufficient to assess clinically meaningful reductions in both maternal depressive and child MI symptoms between groups. Based on the feasibility pilot data, we assume an effect size of *d* = 1.02 in improvement on maternal depression symptoms for both intervention groups (BRIDGE and DBT Skills-Only) [36]. A sample size of *n* = 60 per group will provide very high power (> 99%) to compare intervention groups to SAU. Based on pilot data on child MI symptoms, we assume a within-group SD of 13 on the CBCL and a mean improvement of 14 points [36]. As we anticipate little to no improvement in the SAU arm, we assume an effect size of* d* = 1.08 between BRIDGE and SAU and an effect size of *d* = 0.54 between BRIDGE and DBT-Only (i.e., an effect size 50% smaller than for BRIDGE, based on meta-analyses on the benefit of dual generation programs) [27]. A sample size of *n* = 60 per group will provide very high power (> 99%) to compare BRIDGE with SAU and adequate power (75%) to compare BRIDGE with DBT Skills-only.

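### DBT versus SAU on maternal depression is a stated and powered primary hypothesis, but the analysis section gives it no test and no alpha

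*Protocol article*

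**What the plan says.** The protocol article treats the maternal-depression comparison in five places.

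- **Outcomes {12}** makes it primary: "The primary outcome of this study is mean change in depressive symptoms in mothers from pre- to post-intervention".
- **Objectives {7}**, directly under the primary aim: "We hypothesize that participants who receive the BRIDGE and DBT interventions will report fewer depressive symptoms than participants in the SAU group". For child symptoms the pair differs: "Participants who receive the BRIDGE intervention are hypothesized to report fewer child MI symptoms than those in the DBT and SAU groups". Parenting stress and harsh parenting follow the child-symptom pattern. This section states no BRIDGE vs DBT hypothesis for depression.
- **Explanation for the choice of comparators {6b}**: "the SAU condition will provide insight into whether either intervention is associated with improved outcomes". The interest in BRIDGE vs DBT is described there for child symptoms, parenting stress and parenting behaviors.
- **Sample size {14}** assumes d = 1.02 for "improvement on maternal depression symptoms for both intervention groups (BRIDGE and DBT Skills-Only") and claims "very high power (> 99%) to compare intervention groups to SAU" with 60 per group.
- **Statistical methods {20a}** sets the comparisons for primary, secondary and exploratory outcomes alike: "a) the BRIDGE vs SAU groups and (b) BRIDGE vs DBT-only groups". Each is tested at 0.025, together 0.05.

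Neither DBT vs SAU nor a pooled active-arms vs SAU comparison appears in the analysis sections.

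**The concern.** The two contrasts in {20a} match the hypotheses for child symptoms, parenting stress and harsh parenting. They do not match the depression hypothesis, which needs each active arm compared with SAU. The same pair seems to have been applied to all outcomes without adjustment.

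Two things follow for the PHQ-9. A hypothesis that the protocol states and powers has no named test and no share of the type I error. Half of the error rate goes instead to a comparison for which the sample size section assumes equal effects. The full 0.05 is already allocated, so a DBT vs SAU p-value produced later would be an unplanned test outside the error budget. It would be open to the criticism that it was chosen after seeing the data.

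**Working it through.** **Inputs.** From Sample size {14}: n = 60 per arm; PHQ-9 d = 1.02 for BRIDGE and for DBT, each against SAU; CBCL d = 14/13 ≈ 1.08 for BRIDGE vs SAU and 0.54 for BRIDGE vs DBT. From {20a}: 0.025 per contrast. Sidedness is not stated, so two-sided is assumed and checked in step 1.

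**Method.** Two-sample comparison of means. Noncentrality = d × √(n/2) = d × √30 = d × 5.477, with 2 × 60 − 2 = 118 degrees of freedom. As a normal approximation, power ≈ Φ(noncentrality − z), with z = 2.241 at two-sided 0.025.

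**1. The plan's own figures.**

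| Contrast | d | Noncentrality | Normal approximation | Noncentral t | Stated |
|---|---|---|---|---|---|
| CBCL, BRIDGE vs DBT | 0.54 | 2.958 | Φ(0.716) = 76.3% | 75.3% | 75% |
| CBCL, BRIDGE vs SAU | 1.08 | 5.915 | 99.99% | 99.98% | > 99% |
| PHQ-9, active arm vs SAU | 1.02 | 5.587 | Φ(3.345) = 99.96% | 99.95% | > 99% |

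At two-sided 0.05 the first row would be 83.5% (noncentral t), which does not match the stated 75%. The stated power therefore reproduces with the 0.025 split and a two-sided test, and no stated number is wrong.

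**2. Hypotheses against planned tests.**

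| Outcome | Hypothesized in {7} | Addressed in {14} | Tested under {20a} |
|---|---|---|---|
| PHQ-9 | BRIDGE vs SAU; DBT vs SAU | Both active arms vs SAU | BRIDGE vs SAU; BRIDGE vs DBT |
| CBCL | BRIDGE vs SAU; BRIDGE vs DBT | The same two | The same two |

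The CBCL row is consistent and the PHQ-9 row is not.

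**3. The PHQ-9 test that is planned.** The implied BRIDGE minus DBT effect is 1.02 − 1.02 = 0. At a true difference of zero, a test at 0.025 rejects with probability 2.5%.

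**4. The PHQ-9 test that is missing.** DBT vs SAU at d = 1.02 and two-sided 0.025 has 99.95% power with 60 per arm, and 99.7% if only 50 per arm are analyzed.

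**5. Ways of bringing it in.**

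- Replace BRIDGE vs DBT by DBT vs SAU for the PHQ-9 only: 2 × 0.025 = 0.05, with 99.95% power for each test.
- Add it as a third test at 0.025: the nominal sum is 3 × 0.025 = 0.075. Simulation under the global null, allowing for the shared arms, gives about 0.064, which is still above 0.05.
- Split 0.05 three ways (0.0167 each): DBT vs SAU on the PHQ-9 keeps 99.91%. If the same split were carried over to the CBCL, BRIDGE vs DBT there would fall from 75.3% to 70.1%.

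This is why the contrasts are better set outcome by outcome.

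**The case against.** **The aim concerns BRIDGE, and both planned contrasts serve it.** The primary-aim sentence is indeed worded around BRIDGE. But the DBT vs SAU hypothesis follows directly beneath it, and the sample size section powers it.

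**A statistical analysis plan could settle this.** One may exist and was not available. However, {20a} does not leave the matter open: it fixes contrasts and alpha. A plan that follows it inherits the gap, and one that departs from it contradicts the published protocol.

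**Equal d values are a planning convenience, not a claim of equivalence.** This stands. The 2.5% in step 3 holds for any test when the true difference is zero, and the share given to BRIDGE vs DBT does no measurable harm to BRIDGE vs SAU, which keeps more than 99% power at 0.025. The loss is that DBT vs SAU receives nothing.

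Three stronger readings are tempting and are not supported:

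- *The trial cannot answer the DBT vs SAU question.* All three arms are randomized and measured on the PHQ-9. If one model is fitted to the three arms, DBT minus SAU equals (BRIDGE minus SAU) minus (BRIDGE minus DBT), with a confidence interval. A planned test with an alpha allocation is missing; the estimate is not.
- *The protocol nowhere expects BRIDGE to do better on maternal outcomes.* Dissemination plans {31a} speaks loosely of hypothesized BRIDGE superiority on maternal as well as child outcomes, without naming a comparator. The accurate statement is that Objectives {7} gives no BRIDGE vs DBT hypothesis for depression and that Sample size {14} assumes equal effects.
- *The same defect affects the additional aims (psychopathology, service use, family relationships).* The hypothesis for these names no comparator, and the outcomes are classed as exploratory. The point does not extend to them.

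**Conclusion.** The concern holds for the PHQ-9 as an internal contradiction. Sections {7}, {6b} and {14} agree on BRIDGE vs SAU and DBT vs SAU, and {20a} tests a different pair. As written, one of the two depression hypotheses under the primary aim has no planned test and no alpha, and 0.025 of the 0.05 goes to a contrast with an assumed difference of zero.

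BRIDGE vs SAU on the PHQ-9 and both CBCL contrasts are unaffected. The power figures rest on the plan's d = 1.02, two-sided tests and 60 analyzed per arm. The contradiction itself depends on none of these.

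**What to change.** In {20a}, name the contrasts by outcome.

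- **PHQ-9:** BRIDGE vs SAU and DBT vs SAU, each at 0.025. Report BRIDGE vs DBT as an estimate with a confidence interval and no confirmatory claim. Alternatively, test it only in a prespecified later step of an ordered procedure that keeps the total at 0.05.
- **CBCL, parenting stress and harsh parenting:** keep BRIDGE vs SAU and BRIDGE vs DBT, each at 0.025.

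**Cost.** No new data are needed, and there are still two up-front tests per outcome at the same alpha. The 75% CBCL power is unchanged. The sponsor gives up an up-front confirmatory BRIDGE vs DBT test on the PHQ-9.

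The change also needs an amendment to the Research Ethics Board under {25}. Trial status reports 78 participants randomized and post-intervention assessments under way, and {21b} plans an interim analysis of primary outcomes at about 90 T2 completers. The amendment should therefore be dated before that analysis shows comparative results. If it comes later, it should say so and point to the hypothesis and power statement already published in {7} and {14}.
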